## Intervention

### Implementation strategy

Participants in both trial arms receive a recently developed evidence-based CPG on ROE or MIM. The implementation strategy consists of one interactive IQual group meeting of approximately two to three hours with a minimum of eight GDPs each. These meetings discuss the selected intervention topic, and offer a more risk-based decision-making process guided by the CPG. Topics regarding risk management, such as identification of risk factors/indicators, preventive interventions, prognosis, monitoring, record keeping, and patient scheduling are presented. In addition, all participants receive feedback from personal and group characteristics retrieved from pre-test questionnaire and specific record forms, and are invited to make use of web-based patient risk vignettes for further individual training on risk assessment policy. These risk vignettes were developed by structured consensus procedures (modified Delphi) with expert groups consisted of acknowledged GDPs and oral surgeons in special fields. In addition, reminders (flow charts) and written patient leaflets with topical information are provided during the trial period. Flow charts comprise algorithms of decision-making aspects linked to the trial arm allocation. Depending on the allocated trial arm, participants are subjected to a set of planned interventions as described in Table 2.

**Table 2 T2:** Overview of planned interventions in groups I and II.

**Interventions for all IQualgroups**		
Composition IQual group Introductory letter (individual) Delivery registration forms and questionnaires	Questionnaire GDPs 25 observations chair side	

**Randomisation**		

**Interventions trial arms**	**ROE group I**	**MIM group II**

Delivery CPG on ROE versus MIM by post	CPG ROE	CPG MIM
Education session IQual group	ROE education	MIM education
Online training website (individual feed back)	Access to ROE-based training	Access to MIM-based training
Reminder (flow chart), individual feed back record form Feed back by email	ROE- aspects Flow chart	MIM-aspects Flow chart
Registration in practice (25)	25 observations in practice chair side	25 observations in practice chair side
End trial	Questionnaire	Questionnaire

### Randomisation

After their commitment to participate, 60 GDPs nested in six IQual groups were randomly assigned (using SPSS) as groups to the ROE or MIM arm by an independent secretary not familiar with the groups. The unit of randomisation was the IQUAL group.

### Outcomes and instruments

#### ROE study

Table 3 lists the outcome parameters and instruments used. For the ROE arm, the primary outcome measure is the use and appropriateness of individualised risk assessment measured through the assigned recall intervals (in months). The appropriateness will be assessed as follows:

**Table 3 T3:** Outcome parameters and instruments

**Outcome parameter**		**Instruments**
**Primary ROE-outcomes**	Clinical Performance/decision-making: Number of patients per GDP with assigned recall interval (months) based on individual risk profile assessment. For high-risk children and adolescents' intervals less than seven months, in case of low risk profile more than seven months; for low-risk adults' profiles, nine months equal or more, and for high-risk adults' profiles less than nine months.	**Patient record, registration form, to analyse risk management**
**Secondary ROE-outcomes**	Clinical Performance/decision-making: Number of patients per GDP with prescribed individual frequency of BWs (months). For high-risk children and adolescents, frequencies of less than 24 months, and for low-risk profiles, frequencies of more than 36 months; for high-risk adults, prescription frequencies less than 36 months, and for low risk adults, prescription of more than 48 months. Number of patients per GDP with periodontal DPSI-score > 1, and prevalent caries, who have been given feedback, information and preventive advice, registered in patient record or registration form. Efficacy data/cost-effectiveness scores: Mean overall length in months of recall intervals per GDP over the past 3 yrs Mean total number of BW(s) and other radiographs over past 3 years Type of performer GDP/Oral hygienist/others (level of graduation, education) Total number of additional interventions performed during ROE (polishing, removal of calculus: coded as M50, M55). Professional attitudes and compliance: Measured at the beginning and end of the trial, by questionnaire.	**Patient record, registration form, questionnaire to analyse additional performance and cost-analysis**
**Primary MIM-outcome**	Clinical performance/decision-making: Number of patients (between 17 -35 yr of age) with removed versus retained MIMs in accordance with CPG, or with indication for removal. Number of risk-based assessment radiographs between 17– 35-yrs/per patient with risk-based for assessment of prognosis MIM.	**Patient record, registration form to analyse risk management**
**Secondary MIM-outcome**	Professional attitudes/compliance and feedback: Interviews of patients (17–35 years of age) to confirm risk-based performance.	**Questionnaire**

• For high-risk children and adolescents (0 to 18 years), recall intervals of less or equal than seven months should be assigned. For those with a low-risk profile, an assigned recall of more than seven months is considered appropriate.

• For high-risk adults (18 years and older): recall intervals of less than nine months should be assigned. For those with a low-risk profile, an interval of nine months or longer is considered appropriate.

The secondary outcome measures for the ROE arm are:

1. The use and appropriateness of individualised risk-based assessment in prescribing bitewing radiographs (BWs) in months. The appropriateness will be assessed as follows:

• For high caries-risk children and adolescents (0 to 18 years): BW frequencies of less than 24 months are determined as appropriate; for those with a low-caries risk profile, BW frequencies equal or more than 36 months.

• For high caries risk adults (18 years and older): BW frequencies less than 36 months are determined as appropriate; for those with a low-caries risk profile, BW frequencies of equal or more than 48 months.

2. The use and appropriateness of individualised communication/feedback and advice in patients with a periodontal risk DPSI-score >1, and present dental caries experience. The appropriateness will be assessed as the proportion of patients per GDP receiving appropriate preventive advice/feedback will be calculated. Furthermore, as a secondary outcome measure, professional role perceptions and compliance concerning the recommendations of the ROE-CPG is assessed by means of questionnaires provided at the beginning and end of the study.

3. Resource use will be documented for an economic evaluation:

• The type of recall interval (months) per GDP over the past 3 years

• BW radiographs and other types of radiographs per GDP over the past 3 years

• Type of performer of ROEs: GDP versus oral hygienist/dental auxiliary

• Additional interventions per GDP (i.e. polishing stains/removing dental calculus) encompassed at ROEs over the past 3 years.

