## Methods

### Study design

The study is a cluster-randomised trial with incomplete block design. In one trial arm, the intervention focuses on individual decision-making in scheduling ROEs. In the second arm, the intervention focuses on monitoring and decision-making regarding prophylactic removal versus retention of MIM. Groups of GDPs allocated to either of these arms act as each other's control group. To reduce potential contamination, groups of GDPs are randomised rather than individual GDPs (Table 1). We assumed that the two clinical conditions (or practices) were largely independent of one another, i.e. performing one would not necessarily influence the other. In the ROE arm, the CPG only mentions the necessity of third molars screening in general as routine oral care. In the MIM arm, the CPG provides an extensive, but specific, decision-making algorithm, i.e. how to deal with mandibular asymptomatic impacted third molars.

**Table 1 T1:** Balanced incomplete block design

**Intervention**	**CPG**	
	**ROE**	**MIM**

Group I (ROE)	Intervention	Control
Group II (MIM)	Control	Intervention

Intervention: Clinical Practice Guideline (CPG) on the management of routine oral examinations (ROE) and asymptomatic mandibular impacted third molars (MIM).

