#### MIM study

For the MIM arm, the primary outcome is the use and appropriateness of individualised MIM risk management. The appropriateness will be assessed as follows:

• Patients (17–35 years of age) with removed versus retained MIMs over the past five years as a proportion of patients aged between 17–35 years of age per practice

• Radiographs used for monitoring patients mentioned above to perform a risk-based assessment and prognosis of MIM over the past five years.

A secondary outcome measure is GDPs- attitudes and compliance concerning the recommendations of the MIM-CPG, and relating that information to patients. This measure will use data from patient interviews to confirm risk-based performance.

All data will be collected using special registration forms to be completed by GDPs and patient records available in practices. Questionnaires, patients' records, and registration forms will provide information to assess all outcome parameters. The structured registration forms were used in a previous self-recording study [23].

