### Costs

Costs considered are those used for the implementation (time for participation by GDPs, preparation time, use of materials) and for changes (if any) in professional performance (recall intervals between successive ROEs, total number of radiographs, both based on individual risk assessment). Oral care unrelated to the topic of the interventions within the observed time period will not be considered. Resource use will be extracted from trial data, where possible, or collected separately for the purpose of the economic evaluation. Costs will be valued according to prevailing Dutch guidelines for economic evaluations, and alternatively according to the current national fee-coding list for individual oral treatment procedures in general dental practice.

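### The ROE count and cost of all radiographs can include third-molar films, which the programme in its control arm is meant to change

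*Protocol article*

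**What the plan says.** The Study design section has no untrained arm: "Groups of GDPs allocated to either of these arms act as each other's control group". It supports this with an assumption: "We assumed that the two clinical conditions (or practices) were largely independent of one another". It notes one point of contact between the guidelines, that in the ROE arm "the CPG only mentions the necessity of third molars screening in general as routine oral care".

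Radiographs are counted for both topics.

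- **ROE.** Table 3 lists among the secondary outcomes "Mean total number of BW(s) and other radiographs over past 3 years". The text on ROE resource use has "BW radiographs and other types of radiographs per GDP over the past 3 years". Neither line excludes films taken for third molars.
- **MIM.** Table 3 lists as part of the primary outcome "Number of risk-based assessment radiographs between 17– 35-yrs/per patient with risk-based for assessment of prognosis MIM". The MIM study text has "Radiographs used for monitoring patients mentioned above to perform a risk-based assessment and prognosis of MIM over the past five years".
- **Costs.** The performance-related items are recall intervals and "total number of radiographs, both based on individual risk assessment". The same section leaves out oral care not connected with the subject of the interventions.

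The Statistical analysis section defines the intervention effect as the interaction of allocation and measurement time. The economic Analysis section forms a between-arm incremental cost-effectiveness ratio (ICER) for each topic.

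**The concern.** Using each arm as the other's control isolates one programme's effect only on outcomes that the other programme leaves alone. The independence assumption covers this for the two clinical practices. It does not cover a measure that both topics count. A film taken to assess an impacted third molar is part of what the MIM programme sets out to influence, and as the ROE lines are worded it is also one of the other radiographs in the ROE tally.

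If so, a change in third-molar films brought about by MIM training enters the ROE comparison through its control arm, with the opposite sign. It would be read as an effect of the ROE programme on radiograph use and would enter the cost side of the ROE ICER. Radiographs are one of only two performance-related cost items that the Costs section names.

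**Working it through.** **Plan's own figures.** The protocol gives no radiograph rate or expected change, so there is no figure on this point to reproduce. Its sample size does reproduce. For 20% against 40%, two-sided alpha 0.05 and 80% power, 82 patients per arm are needed before clustering. The design effect is 1 + (150 − 1) × 0.03 = 5.47, and 82 × 5.47 = 448.5, against a stated 450 per arm. That calculation concerns the primary outcomes and is unaffected here.

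**What the contrast estimates.** On a linear scale, let t be the change over time common to both arms, r the ROE programme's effect on the counted radiographs per patient, m the MIM programme's effect per patient it can reach, and s the share of patients in the ROE count whom it can reach.

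- Change in the ROE arm: t + r
- Change in the MIM arm: t + s × m
- Interaction: (t + r) − (t + s × m) = r − s × m

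The baseline measurement removes t and any difference between arms at the start. It does not remove s × m, which arises after baseline and only in the control arm. The contrast equals r only if s or m is zero.

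**Illustration (r, m and s all assumed).** Entries are films per patient, ROE arm minus MIM arm.

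| s | r = −0.20, m = −0.20 | r = −0.20, m = +0.20 | r = 0, m = −0.20 | r = 0, m = +0.20 |
|---|---|---|---|---|
| 0.10 | −0.18 | −0.22 | +0.02 | −0.02 |
| 0.25 | −0.15 | −0.25 | +0.05 | −0.05 |
| 0.50 | −0.10 | −0.30 | +0.10 | −0.10 |
| 1.00 | 0.00 | −0.40 | +0.20 | −0.20 |

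**A narrower range.** Assume r = 0, m = ±0.2, and that 20% to 30% of counted patients are aged 17 to 35 and all can be reached. Then 0.2 × 0.20 = 0.04 and 0.2 × 0.30 = 0.06, that is 4 to 6 films per 100 patients, opposite in sign to m.

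**Effect of the look-back.** The Timeframe section starts the intervention in months two and three and collects follow-up in months eight to ten. Between 8 − 3 = 5 and 10 − 2 = 8 months of a 36-month window then follow the intervention: 5/36 = 14% to 8/36 = 22%. If 0.2 is the effect over a full window, the figures become 0.04 × 5/36 = 0.0056 and 0.06 × 8/36 = 0.0133, about 0.6 to 1.3 films per 100 patients. The MIM inclusion criteria also require disease-free impacted mandibular third molars, which lowers s further. The look-back dilutes r in the same way, so it shrinks the contrast without separating the two effects.

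**The case against.** The strongest reply is that the economic plan already has a safeguard. The Costs section drops unrelated oral care and ties the radiographs to individual risk assessment, and an ICER is formed for each topic. Read together, third-molar films could be off-topic for the ROE ICER. This stands to the extent that a reader should not infer that the Costs section contradicts itself. But it speaks of the interventions together and does not say that relatedness is judged topic by topic. Third-molar films are related to one of the two, so they are not clearly removed. Nor does the safeguard reach the ROE secondary outcome in Table 3.

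A second reply is that the ROE text already names bitewings apart from other films, and that coding and attribution rules belong in registration forms or a fuller plan. The absence of such coding is indeed no finding. The point rests on what the article does fix: a combined total in Table 3, the other arm as control, and a between-arm contrast.

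Third, the size is assumed throughout, and the look-back and the restriction to impacted molars make it smaller. That stands.

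Fourth, the evaluation takes a healthcare perspective, so dropping non-bitewing films could discard a real ROE effect. That is a true cost of the remedy.

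**Conclusion.** The point holds for three items only: non-bitewing radiographs, total radiographs, and the radiograph cost in the ROE ICER where it uses the total. For these the contrast is the ROE effect minus the MIM effect. This follows from the outcome definitions, the choice of control and the definition of the intervention effect. It assumes that third-molar films fall within the ROE count, which the wording permits, and that the MIM programme changes them. Size and sign cannot be derived from the documents and may be small.

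A reader might infer that the cross-control design fails. The documents do not support that. Recall-interval, bitewing and preventive-advice outcomes are not shown to be affected. The effect measure of the ICER is professional performance (Effectiveness section), not film counts, so it is untouched too. The MIM radiograph outcome is confined to third-molar films and is less exposed, although the ROE guideline's mention of third-molar screening touches it.

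Nor should the point be put as a lost comparison with usual care. The Scientific hypothesis section names dissemination of guidelines alone as the comparator.

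**What to change.** 1. Separate radiographs by type at record extraction, and by indication where the records allow.
2. Base the ROE radiograph comparison and the radiograph cost in the ROE ICER on bitewings, or on all films other than third-molar films.
3. Base the MIM radiograph outcome and its cost on films taken to assess the mandibular third molar.
4. State in the Costs section that whether care is unrelated is judged separately for each topic's ICER.
5. Report total radiographs only as a descriptive comparison of the two programmes or as a sensitivity analysis.

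The cost is some rewording and a small coding effort, since extraction from patient records is already planned. The documents do not say whether those records hold the indication; where they do not, the split by type still serves. Any true ROE effect on the excluded films is no longer claimed in the main comparison. The option of excluding only third-molar films keeps more of it than bitewings alone. The sample size does not change.

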#### MIM study

For the MIM arm, the primary outcome is the use and appropriateness of individualised MIM risk management. The appropriateness will be assessed as follows:

• Patients (17–35 years of age) with removed versus retained MIMs over the past five years as a proportion of patients aged between 17–35 years of age per practice

• Radiographs used for monitoring patients mentioned above to perform a risk-based assessment and prognosis of MIM over the past five years.

A secondary outcome measure is GDPs- attitudes and compliance concerning the recommendations of the MIM-CPG, and relating that information to patients. This measure will use data from patient interviews to confirm risk-based performance.

All data will be collected using special registration forms to be completed by GDPs and patient records available in practices. Questionnaires, patients' records, and registration forms will provide information to assess all outcome parameters. The structured registration forms were used in a previous self-recording study [23].

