**Methods/design:**

This study is a cluster randomised controlled trial with groups of GDPs as the unit of randomisation. The aim is to determine the effectiveness and efficiency of small group quality improvement on professional decision-making of general dental practitioners (GDPs) in daily practice. Six peer groups ('IQual-groups') shall be randomised either to the intervention arm I or arm II. Groups of GDPs allocated to either of these arms act as each other's control group. An IQual peer group consists of eight to ten GDPs who meet in monthly structured sessions scheduled for discussion on practice-related topics. GDPs in both trial arms receive recently developed evidence-based clinical practice guidelines (CPG) on ROE or MIM. The implementation strategy consists of one interactive IQual group meeting of two to three hours. In addition, both groups of GDPs receive feedback on personal and group characteristics, and are invited to make use of web-based patient risk vignettes for further individual training on risk assessment policy. Reminders (flow charts) will be sent by mail several weeks after the meeting.

The main outcome measure for the ROE intervention arm is the use and appropriateness of individualised risk assessment in assigning recall intervals, and for the MIM-intervention group the use and appropriateness of individualised mandibular impacted third molar risk management. Both groups act as each other's control. Pre-intervention data will be collected in study months one through three. Post-intervention data collection will be performed after nine months.

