### Data collection

After their informed consent to participate, GDPs will be invited to first complete a questionnaire to collect personal and practice characteristics, as well as aspects of attitude and compliance. Individual assessment of electronic patient records with regard to the outcome measures, combined with a special registration form (to be applied individually in daily practice), will be used during the evaluation period.

Baseline information will be collected before randomisation of groups, as well as at the end of the trial after seven to nine months. Each GDP will be instructed to complete at least 20 forms per registration period. As each peer group consists of at least eight participants, and each arm will consist of three groups, this will result in a minimum of 480 registrations per trial arm. Finally, questionnaires will be collected from GDPs, dentist's assistants and co-workers to assess acceptance and applicability.

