## Economic evaluation

An economic evaluation is performed to estimate the cost-effectiveness of the implementation intervention. This study takes a healthcare perspective and a time horizon that is similar to the implementation trial.

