### Timeframe of the study

We plan to randomise six of the initially recruited IQual groups that have declared their willingness to participate in this study, and to assign them randomly to one of the two intervention arms. The baseline data collection will take place at the beginning of the study during months one and two. The intervention will start in months two and three, and follow-up data collection will be collected in months eight through ten. The scheduled time for the trial is estimated to be seven to ten months (Appendix 1), assuming that each GDP will collect data from at least 20 regular attending patients by means of the trial registration form.

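### The MIM primary measures look back five years and the ROE resource items three, with no separate post-intervention window, although follow-up comes only 5–8 months after the intervention

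*Protocol article*

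**What the plan says.** All references are to the protocol article.

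- **MIM study (primary outcome).** The first measure counts patients "with removed versus retained MIMs over the past five years as a proportion of patients aged" 17 to 35 in each practice. The second counts radiographs used "to perform a risk-based assessment and prognosis of MIM over the past five years".
- **Table 3 (same primary outcome).** Removal or retention is scored for agreement with the guideline, and no look-back window is given.
- **ROE study (resource use).** The list includes "The type of recall interval (months) per GDP over the past 3 years" and "BW radiographs and other types of radiographs per GDP over the past 3 years", and additional procedures over the same three years.
- **Timeframe of the study.** "The intervention will start in months two and three, and follow-up data collection will be collected in months eight through ten". Data collection describes the second measurement "as well as at the end of the trial after seven to nine months", and the abstract says "Post-intervention data collection will be performed after nine months".
- **Statistical analysis.** The intervention effect is the interaction of allocation with measurement time (baseline, post-intervention). One outcome definition serves both times.
- **Patient criteria.** Patients need three years of regular attendance. For MIM, the third molars must still be in place, and patients whose third molars were removed earlier are excluded.
- **Economic evaluation.** It takes "a time horizon that is similar to the implementation trial".

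**The concern.** A follow-up measurement can show an effect only through care given after the intervention. A five-year count made 5–8 months after the education session consists mostly of care that the session could not have altered. The same earlier care also fills most of the baseline count. The interaction term would then compare two largely overlapping histories, and a working intervention could look ineffective on the MIM primary outcome. The three-year resource counts would shrink the cost difference in the incremental cost-effectiveness ratio in the same way.

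The five-year window also fits poorly with other parts of the article. It is longer than the attendance that eligibility guarantees. It counts removals in patients who, under the exclusion criteria, should have had none. And it differs from the definition of the same outcome in Table 3.

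**Working it through.** **The plan's own figure.** Sample size aims for a 20-point change for both interventions and arrives at 450 registrations per arm. This reproduces: 20% against 40% with 80% power and two-sided alpha 0.05 (sidedness assumed) needs 82 independent patients per arm. The design effect is 1 + 149 × 0.03 = 5.47, and 82 × 5.47 = 448.5. That figure is not in question here. It allows for no loss of effect through the measurement window.

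**Inputs.** Intervention in months 2–3 and follow-up in months 8–10 (Timeframe of the study); look-back of 60 months (MIM study) and 36 months (ROE study, resource use).

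**Elapsed time.** Shortest 8 − 3 = 5 months; longest 10 − 2 = 8 months.

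**Share of the follow-up window after the intervention** = elapsed months ÷ window length, if care is spread evenly:

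| Elapsed | MIM, 60 months | ROE resources, 36 months |
|---|---|---|
| 5 months | 5/60 = 8.3% | 5/36 = 13.9% |
| 8 months | 8/60 = 13.3% | 8/36 = 22.2% |
| 9 months (longest reading of the abstract) | 9/60 = 15.0% | 9/36 = 25.0% |

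The pre-intervention share is therefore 87–92% for MIM and 78–86% for the ROE resource items. Even on the longest reading of the abstract it is 85% and 75%.

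**Overlap of the two MIM windows.** Timeframe of the study puts baseline in months 1–2, so the two measurements are 8 − 2 = 6 to 10 − 1 = 9 months apart. Two five-year windows then share 60 − 9 = 51 to 60 − 6 = 54 calendar months, or 85–90%.

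**Illustration for MIM only.** Under even spread, a true 20-point change in post-session care would appear as 20 × 5/60 = 1.7 to 20 × 8/60 = 2.7 points.

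**The other reading.** If the look-back belongs to baseline alone, a 60-month count is set against a 5–8 month count. The baseline window is then 60/8 = 7.5 to 60/5 = 12 times as long, and the time term in the model mixes change in care with change in exposure.

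**The case against.** No sentence says that the look-back is repeated at follow-up. The Analysis part of the economic evaluation mentions retrospective sampling next to the pre-test data and names post-intervention data separately, so the histories may have been meant for baseline only. This stands, and it makes the dilution conditional. It does not rescue the plan, because no follow-up window is given and the two measurements would then differ in length.

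Table 3 already offers a definition without a window, and new chairside forms are completed in both registration periods. That also stands, but the MIM study section states a different definition of the same primary outcome, and nothing says which prevails. A condensed article may leave extraction detail to the full protocol; here, however, the window is printed as part of the primary outcome.

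The even-spread model ignores eligibility. If patients with earlier removals are excluded from the count, past removals cannot fill the window as assumed, and 8–13% is not exact for the removal measure. If instead all practice patients aged 17–35 are counted, the three-year attendance rule may not be the relevant limit. Three years is in any case a minimum, so many records may reach back five; the criteria only fail to guarantee it.

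Recording a three-year history does not in itself contradict a trial-length horizon, and the Costs section allows separate collection. The mismatch bites if those counts feed the cost-effectiveness ratio.

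Three stronger conclusions are tempting, and the article supports none of them:

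- **Power for MIM falls close to alpha.** The 20-to-40% example concerns recall intervals, no MIM base rate is given, and overlapping windows would correlate baseline with follow-up and change the precision of the interaction.
- **The 20-point target can be translated to the ROE resource items.** These are mainly mean intervals and counts, not the proportion used in the sample size.
- **The trial as a whole cannot show an effect.** The ROE primary outcome is the interval assigned at the visit and has no look-back.

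**Conclusion.** The point holds in conditional form. As defined, both MIM primary measures cover five years and the ROE resource items three, with no post-intervention window. If the definition is applied unchanged at follow-up, as the interaction model implies, only about 8–13% of the MIM window and 14–22% of the ROE resource window can reflect the intervention. The MIM primary effect and the cost difference are then strongly diluted towards zero. If the look-back is for baseline only, unequal windows are compared. Either way the MIM primary outcome is not fixed in a form that the planned model can use.

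The shares rest on the months in Timeframe of the study and on care spread evenly over the window. The direction needs only that much of the counted care precedes the session. Separately, the five-year window has to be reconciled with Table 3, the three-year attendance rule and the exclusion of earlier removals, and the three-year resource counts with the trial-length economic horizon.

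**What to change.** 1. Reconcile the MIM study section with Table 3 by using the Table 3 wording, agreement of the decision with the guideline, for the MIM primary outcome.
2. At follow-up, count only decisions, radiographs and procedures dated after that group's education session.
3. Use a baseline window of the same length immediately before the session, so that both levels of the time factor measure the same quantity.
4. Keep the three- and five-year histories as baseline descriptors only.
5. Match the resource-use window for the economic evaluation to the trial horizon.

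The extra work is a date filter on records that are already to be assessed, plus revised outcome wording. The real price is statistical: a window of 5–8 months holds few removals and radiographs, and many patients will have at most one recall visit in it. There will be fewer events per patient, and some measures will be less precise.
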